
### Measuring Accessibility and Inclusion

#### GoPro Cameras

The use of GoPro cameras (GoPro Inc, HERO12 Black) captures visual and audio data of children’s perspectives and their unique play behaviors at the outdoor-focused ELCC program. GoPro cameras will be worn by children with and those without disabilities to compare play behaviors and physical activity participation. GoPros are placed on the child using the GoPro Junior Chesty (GoPro Inc, Junior Chest Mount Harness), which is designed for children ages 3‐14 years old weighing between 25 and 115 pounds. The use of chest-supported mounted GoPro cameras is deemed feasible in children aged 17‐25 months without impediment of balance due to additional weight [58]. Data collection occurs for approximately 1 to 2 hours during ELCC. Children are introduced to the GoPro cameras during a familiarization period prior to data collection. They are introduced to assessors who are present during times of collection and who invite them to wear a camera if they want to. During this familiarization period, all children are allowed to explore the GoPro cameras and chest straps to become familiar with the equipment. Throughout data collection, assessors and staff remain nearby in the event that children’s expressions or nonverbal cues suggest they are no longer comfortable wearing the GoPro cameras. Children are allowed to request to stop wearing the camera at any moment through any means of communication (eg, verbally, photo exchange communication). Audio and video collected from the GoPro cameras are uploaded to a secure institutional server accessible only to the research team at the end of each data collection session and are erased from GoPro storage. Given that there is a possibility of children and educators not participating in the study being captured on the GoPro footage, all caregivers of children and educators at the outdoor-focused ELCC will be notified about the research study. Only children who provide consent (ie, wear the GoPro) will be included in the analysis. Analyses will focus on each consenting child’s behavior independently, without directly coding or describing the behaviors of others (eg, noting that a child began playing following a positive or negative peer interaction, rather than detailing the peer’s specific actions).

All video and audio recordings will be deidentified (eg, names removed from audio transcripts). Video footage will be used for analysis purposes only, and no video footage will be shared publicly or beyond the research team. Once the video is analyzed and the study is complete, the video footage will be destroyed.

#### Educator, Caregiver, and Community Partner Feedback

To gather ongoing feedback on accessibility and inclusion as well as feasibility and acceptability at the outdoor-focused ELCC center, we collect annual qualitative data using World Café focus groups and individual interviews with caregivers and educators. The World Café method is a structured, participatory approach that facilitates collaborative dialogue through a series of small-group discussions focused on key questions [59]. Participants rotate between 3 to 5 tables, 20 minutes at a time, with each table addressing a specific aspect of accessibility and inclusion. Participants are invited to contribute using a variety of communication tools: speaking, writing on sticky notes, and molding with clay. A designated host remains at each table to summarize previous conversations and support continuity across groups. This method allows for the collection of diverse perspectives in an inclusive and conversational format. Insights generated through qualitative data collection will be synthesized and used to inform annual modifications to the program, ensuring it remains responsive to the needs of the community. World Café focus groups will be conducted once every 2 years.

In addition to World Café focus groups, semistructured one-on-one interviews will be conducted with caregivers and educators to explore the acceptability and feasibility of the outdoor-focused program, the barriers and facilitators to inclusive and accessible outdoor play, and their perceptions of the program’s impact on children’s development. The interviews will be guided by an interview guide that consists of 16 questions, each with a corresponding set of prompts. Within the interview guide, caregivers and educators will be prompted to discuss their perspectives on the children’s experiences at the outdoor-focused program and their views on children’s physical, cognitive, and social-emotional development since beginning the program. Caregivers and educators will also be prompted to discuss the barriers and facilitators to outdoor play that children with and those without disabilities face in the outdoor-focused program. Each interview will take approximately 45‐60 minutes to complete and will be conducted on Zoom (Zoom Communications, Inc). The interviews will be audio and video recorded; however, only audio files will be retained for study purposes. Interviews will be conducted yearly and will prioritize caregivers of children in the SPROUT-able substudy.

### Data Analysis Plan: Primary Objective and Secondary Objectives 1 and 2

Descriptive statistics are used to summarize participant characteristics and all primary measures, including developmental assessments, movement behaviors, caregiver attitudes, support behaviors, and educator outcomes. Means and SDs are reported for continuous variables, and frequencies and percentages for categorical variables. General linear mixed-effects models will be used for the primary objective and secondary objectives 1 and 2 to examine differences in change over time and between groups. Separate models will be specified for child developmental outcomes (eg, motor, cognitive, and social-emotional), movement behaviors (eg, physical activity, sedentary time, and sleep), caregiver attitude and support measures, and educator-reported measures (eg, job satisfaction, health and well-being, and attitudes toward outdoor play). Models will include fixed effects for time (eg, T0 and T1), group (experimental vs usual care), and relevant covariates (eg, child age, sex, disability status, race and ethnicity, parent income, parent education, and newcomer status). For covariates with small subgroup sizes, distributions will be examined prior to modeling; where sparse categories are identified, categories will be collapsed as appropriate to ensure stable estimation. A random effect for participant (study ID) will be included to account for within-subject correlations across time points. The primary analyses will treat the 3 usual care sites as a single group. Sensitivity analyses will additionally adjust for the ELCC site (included as a fixed effect) to examine potential differences between individual usual care centers and to evaluate the extent to which such differences may influence the results.

Interaction terms (eg, group × time) are tested to examine whether changes over time differ between the experimental and usual care group, thereby estimating intervention effects as differences in change from baseline. Because baseline measurements are included as part of the repeated outcome in the mixed-effects models, this approach inherently adjusts for baseline differences between groups. The mixed-effects models accommodate unbalanced data, such that participants are not required to have observations at all time points; individuals with missing baseline or follow-up measurements contribute all available data to the analysis. These missing time points are handled within the maximum likelihood framework under a missing at random assumption, avoiding listwise deletion. Missing data within completed measurement occasions (eg, partial or item-level missingness) will be explored and, where appropriate, addressed using additional methods (eg, multiple imputation) based on the nature and extent of missingness. Model assumptions are checked using residual diagnostics. Statistical significance is set at less than *P*=.05. Effect sizes are computed and interpreted using established guidelines, with CIs reported to aid interpretation of both statistical and practical significance. Interim analyses are conducted after each year of the study and final analyses will be conducted after all data collection is complete (Figure 1). All analyses are conducted in R version 4.4.2 [28] using RStudio version 2024.12.0+467 [29].

### Secondary Objective 3

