### Ethical Considerations

This study has received institutional research ethics board approval (#23/108X). Caregiver-child dyads and educators consent to 1 year of the study and are encouraged to reenroll for up to 2 years as long as the child remains at the center (refer to Figure 1 for study timeline).

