**Figure 3. F3:**
[figure not shown]
Images of the outdoor space at the conventional Early Learning and Child Care programs (ie, usual care sites).

A priori power analysis was conducted using G*Power (Heinrich-Heine-Universität Düsseldorf) to estimate the sample size required to detect meaningful group differences over time for the primary objective of the study (ie, child outcomes). Given the complexity of general linear mixed-effects models and the limited availability of accessible power calculation tools for these models, a repeated-measures ANOVA with a within-between interaction was used as an approximation. This approach allows for estimating power to detect changes within participants over 3 time points and differences between 2 groups (experimental vs usual care). The calculation assumed a small effect size (*f*=0.20), a power of 0.80, and an alpha level of .05. This choice aligns with findings from systematic reviews indicating that ELCC interventions often yield small but statistically significant effects on children’s development [24]. Based on these parameters, the estimated required sample size is 42 child participants (21 per group). While our primary analyses use general linear mixed-effects models, this conservative ANOVA-based estimate provides a reasonable benchmark for planning purposes and may underestimate statistical power. Given the open cohort design, in which participants may enter and exit over time and contribute varying numbers of observations, precise specification of variance and correlation parameters is challenging at the design stage. In the absence of prior data, assumptions were therefore based on conservative estimates. To further strengthen these estimates, an internal pilot approach will be used whereby preliminary data from the first year of the study (ie, Wave 1: T0, T1, and T2) will be used to estimate key parameters (eg, variance components and within-subject correlation). These estimates will inform a refined assessment of sample size and statistical power for the remaining study period. This process will not involve formal hypothesis testing and will not affect the integrity of the primary analyses. The current sample size estimation is treated as a minimum threshold. In practice, we aim to enroll 100% of children attending the outdoor-focused ELCC center (ie, experimental site) and seek to match this number across the usual care sites. Therefore, we anticipate a substantially larger sample size that will improve the precision and generalizability of our findings [25].

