Assessments with children take place on-site during ELCC hours 3 times per year: baseline (T0), 6-month follow-up (T1), and 12-month follow-up (T2). For children who reenroll in the study after 1 year, assessments will continue every 6 months for up to a total of 6 follow-up assessments. There will be 3 waves of data collection representing 3 cohort groups across 3 years (Figure 3). Important to note, “waves” are distinct from time points; time points (eg, T0 and T1) refer to when data are collected during the study, whereas waves refer to when groups of participants are enrolled in the study. Testing of all children is typically completed over a 1-month period in the summer (August) and winter (February). To support children’s understanding of the research activities and to promote their engagement, a Research Garden (Figure 4) was created at the experimental ELCC program. This space offers a welcoming, familiar environment where children can explore materials, ask questions, and participate in tasks more comfortably. By embedding the research within an inviting, playful setting, the Research Garden helps motivate children, reduce apprehension, and foster a sense of curiosity and involvement in the study. Although we were unable to establish a Research Garden at usual care sites, we support children’s engagement through regular visits to the center to build familiarity with the research team. We also worked with the educators to select a temporary, quiet, child-friendly space for assessments and will use the same space for future assessments to build comfort. We also use engaging materials (eg, a teddy bear wearing an accelerometer) and small incentives (eg, stickers) to promote participation.

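### The single participant random effect, read as a random intercept, understates the uncertainty of long-term group × time effects if children's growth rates differ

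*Protocol article*

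**What the plan says.** The section Data Analysis Plan: Primary Objective and Secondary Objectives 1 and 2 fixes the model as follows.

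- **Fixed part:** "Models will include fixed effects for time (eg, T0 and T1), group (experimental vs usual care), and relevant covariates".
- **Random part:** "A random effect for participant (study ID) will be included to account for within-subject correlations across time points". No other random term or residual correlation structure is named.
- **Site:** it enters only as a fixed effect in a secondary analysis: "Sensitivity analyses will additionally adjust for the ELCC site (included as a fixed effect").
- **Treatment effect:** the group × time interaction, "thereby estimating intervention effects as differences in change from baseline".
- **Model checking:** "Model assumptions are checked using residual diagnostics". No rule says what changes if the check fails.

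On length of follow-up, Data Collection Procedures says that for children who re-enroll "assessments will continue every 6 months for up to a total of 6 follow-up assessments", so at most 7 assessments with baseline. Ethical Considerations makes this a ceiling: families "consent to 1 year of the study and are encouraged to reenroll for up to 2 years as long as the child remains at the" childcare site.

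**The concern.** A random intercept lets children differ in level but not in rate of change. Any two assessments of a child then have the same correlation, whether 6 months or 3 years apart. The cohort enters at 10 to 59 months of age, with and without disabilities, so differing developmental rates are plausible.

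The interaction is a comparison of change. Variation in growth between children adds to the true variance of that comparison, but under an intercept-only model it is absorbed as ordinary residual noise and not carried fully into the standard error. The discrepancy grows with the length of the series. The interaction is the effect on which the primary objective turns. The Strengths and Limitations section also relies on differences in change over time to answer selection bias. Its standard error is therefore the one that most needs to be right.

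**Working it through.** **Inputs from the document.** Enrolment of 67 experimental and 43 usual care children (Results), assessments 6 months apart, at most 7 per child.

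**Assumptions, because the document gives none.** Residual variance s² = 0.30, intercept variance 0.49, between-child slope SD d = 0.1 to 0.4 SD/year. For the open cohort, 60/25/15% of children have 3/5/7 assessments.

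**The plan's own figure.** The sample size of 42 uses f = 0.20 with "a power of 0.80, and an alpha level of .05", 3 time points and 2 groups. With correlation 0.5 and sphericity (neither is stated) it reproduces: power is 0.803 at N = 42 and 0.782 at N = 40. It covers 3 assessments only and says nothing about longer series.

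**Linear time, equal number m of assessments.** Let Sxx be the sum of squared deviations of the assessment times, in years. The true variance of the interaction is proportional to s² + d²·Sxx. The intercept-only model instead reports s² + d²·Sxx/(m − 1). The SE ratio r (true/reported) is the square root of their quotient, and type I error is 2·[1 − Φ(1.96/r)].

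- *3 assessments* (0, 0.5, 1 year; Sxx = 0.5), d = 0.4: true 0.30 + 0.16 × 0.5 = 0.38; reported 0.30 + 0.16 × 0.25 = 0.34; r = √(0.38/0.34) = 1.06; error 6.4%.
- *7 assessments* (0 to 3 years; Sxx = 7), d = 0.3: true 0.30 + 0.09 × 7 = 0.93; reported 0.30 + 0.63/6 = 0.405; r = √(0.93/0.405) = 1.52; error 19.6%.

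**Visit-coded time, 7 assessments, d = 0.3.** The true variance of change from T0 to time t is proportional to 2s² + d²t². The model reports 2 × 0.405 = 0.81 for every visit.

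- T1 (0.5 year): 0.60 + 0.0225 = 0.6225, ratio √(0.6225/0.81) = 0.88, interval too wide.
- T3 (1.5 years): 0.60 + 0.2025 = 0.8025, ratio 1.00.
- T6 (3 years): 0.60 + 0.81 = 1.41, ratio 1.32, interval too narrow.

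**All settings.** For the mix, the intercept-only model was fitted to its large-sample limit and its reported variance compared with the sandwich variance. Entries are type I error for a nominal 5% test.

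| Assessments | Time coding | d = 0.1 | 0.2 | 0.3 | 0.4 |
|---|---|---|---|---|---|
| 3 each | linear | 5.1% | 5.4% | 5.8% | 6.4% |
| 3 each | by visit, omnibus | 5.0% | 5.0% | 5.0% | 5.0% |
| 60/25/15 mix | linear | 6.7% | 11.6% | 18.0% | 24.3% |
| 60/25/15 mix | by visit, omnibus | 5.6% | 7.5% | 10.7% | 14.4% |
| 7 each | linear | 7.2% | 13.0% | 19.6% | 25.1% |
| 7 each | by visit, omnibus | 5.1% | 5.5% | 6.6% | 8.0% |

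In the mix at d = 0.3, the visit-specific SE ratios from T1 to T6 are 0.93, 0.98, 1.05, 1.16, 1.23 and 1.39. At d = 0 every entry is 5%.

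**Simulation check.** With linear time, the mix and d = 0.3, the intercept-only model rejected in 16.3% of 300 null runs. With a random slope added, 4.7% of 150 runs rejected.

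**The case against.** **The document does not say intercept only.** It neither uses the word intercept nor excludes a slope, and an article may leave covariance detail to a fuller plan. This limits how firmly the point can be put. But the article does describe the random part, and gives one participant effect as its account of within-subject correlation. The natural reading of that is an intercept, so the point concerns something stated.

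**Time looks coded by visit.** A reader might infer that every group × time interval is too narrow, or that the tested effect is a slope. The document supports neither. It writes time as T0 and T1 and defines the effect as change from baseline, without fixing the coding. Under visit coding the early contrasts are slightly conservative, and the omnibus error is well below the linear-time figure. This objection stands. What remains is inflation at late visits and in the unbalanced mix.

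**The driver is assumed.** This also stands. Slope variance may be small for age-standardized scores, and nothing in the document shows large stable differences in growth for accelerometry or sleep outcomes. At d = 0.1 the error in the mix is only 6.7% (linear) or about 5.5% (omnibus).

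**Long series will be limited.** Consent is yearly, later entrants cannot reach 7 assessments, and several tasks start at 36 months while mean baseline age is 29.8 months. For outcomes with about 3 assessments the problem is negligible.

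**Wave 1 estimates and residual diagnostics are planned.** They could reveal the problem, but neither is tied to a change of model.

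**Conclusion.** The point holds conditionally. On the natural reading, the stated model gives wrong standard errors for group × time whenever children's growth rates differ. The error is anti-conservative for a linear time effect and for contrasts at about T4 to T6, neutral or slightly conservative for early contrasts, and negligible with 3 assessments.

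In the assumed open-cohort mix, a nominal 5% test has a true error of about 7 to 24% (linear time) or about 5.5 to 14% (visit-coded omnibus) over slope SDs of 0.1 to 0.4 SD/year. These ranges depend on an assumed slope variance and visit mix, so they show what is possible and do not predict the error of any one outcome. A blanket statement that all interaction intervals are too narrow, or that every child outcome is affected, would go beyond the document. The point deserves action because long-term change is what a 3-year study is for, and the remedy is cheap.

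**What to change.** For child outcomes with more than 3 assessments, replace the intercept-only structure:

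- **Linear time:** a random intercept plus a random slope for time.
- **Visit-coded time:** an unstructured or autoregressive within-child covariance.
- **If the fit fails:** participant-clustered robust standard errors with a small-sample correction.

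State which coding of time is used, since the choice of structure depends on it. Choose the structure from the Wave 1 variance-component and within-subject correlation estimates that the Participants and Settings section already plans to obtain without hypothesis testing. Outcomes with about 3 assessments can keep the present model.

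The cost is one change of model term, somewhat wider intervals for long-term effects, and an occasional non-convergent fit.

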**Methods:**

This prospective longitudinal open cohort study follows children, caregivers, and educators over 3 years. Participants are recruited from 1 outdoor-focused (experimental) and 3 conventional (usual care) ELCC centers in Ontario, Canada; all sites are licensed. Assessments occur every 6 months and include direct measures of children (eg, anthropometry, motor skills, and accelerometry) and caregiver and educator questionnaires. Mixed-effects modeling will examine changes over time and between groups (experimental vs usual care).

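### The planned site adjustment acts on outcome levels, so it hardly touches group × time and cannot show whether differences in change between centers drive the result

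*Protocol article*

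**What the plan says.** The Abstract (Methods) gives the structure: "Participants are recruited from 1 outdoor-focused (experimental) and 3 conventional (usual care) ELCC centers in Ontario, Canada". The Data Analysis Plan for the primary objective and secondary objectives 1 and 2 then sets the model. On fixed effects: "Models will include fixed effects for time (eg, T0 and T1), group (experimental vs usual care), and relevant covariates". On random effects: "A random effect for participant (study ID) will be included to account for within-subject correlations across time points". No random effect for center is listed. On pooling: "The primary analyses will treat the 3 usual care sites as a single group".

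The effect of interest is the group × time interaction, "thereby estimating intervention effects as differences in change from baseline".

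The one analysis that deals with center is a sensitivity analysis: "Sensitivity analyses will additionally adjust for the ELCC site (included as a fixed effect) to examine potential differences between individual usual care centers". A second purpose follows in the same sentence: "to evaluate the extent to which such differences may influence the results". No site × time term is mentioned.

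**The concern.** Every child in the experimental group attends the same center, so knowing the site means knowing the group. Adding site to a model that already contains group makes one column redundant. What site then adds is a constant shift for each usual care center. The intervention effect is a difference in change, and a constant shift within a center drops out of a change.

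The check would therefore return nearly the same group × time estimate and standard error as the primary model, even if the three usual care centers changed at very different rates. A reader would take that agreement as evidence that center does not matter.

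The primary model raises a related question. With only a participant random effect, it treats variation between centers in change over time as zero. If that variation is not zero, the test is too liberal for a claim about outdoor-focused programs in general.

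**Working it through.** **Inputs from the protocol.** One experimental and three usual care centers. Three time points (T0, T1, T2) in the power calculation and the first year. In Results: 39 experimental and 23 usual care children with T0, T1 and T2; 18 late entrants without T0 (13 and 5); 67 and 43 children currently enrolled. Licensed places at the usual care centers: 49, 39 and 31.

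**Assumed, because the protocol does not give them.** Usual care children per center: 8/8/7 for the 23; for the 43, 18/14/11 in proportion to licensed places (43 × 49/119 = 17.7; 43 × 39/119 = 14.1; 43 × 31/119 = 11.2). Site-by-time share p of the variance in change: 1%, 2%, 5%, 10%.

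**Step 0. The plan's own figure.** The sample size of 42 uses a within-between interaction with f = 0.20. The noncentrality is f² × N × m/(1 − ρ) = 0.04 × 42 × 3/0.5 = 10.08 with 2 and 80 df, which gives power 0.803. N = 42 is reproduced if the correlation ρ is 0.5, a value the article does not state. No allowance for center enters this figure.

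**Step 1. Rank of the fixed-effects design (three categorical time points).**

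- Time, group, group × time: 6 columns, rank 6.
- The same plus three site indicators: 9 columns, rank 8. One column is redundant.
- The same plus site × time: 15 columns, rank 12. The group terms add nothing to site.
- Time, site and site × time without group terms: 12 columns, rank 12. This model is estimable.

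**Step 2. Does the site adjustment move group × time?** Data were simulated with a site SD of 0.5 in levels and fitted with and without the two estimable site contrasts.

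- Complete data, 39 vs 8/8/7, with site differences in change also simulated: the largest shift at T2 was 4 × 10⁻¹⁵, that is, zero.
- With the 18 late entrants, the 5 usual care ones spread 2/2/1: the SD of the shift was 0.001 to 0.007 for ρ from 0.8 to 0.3.
- With all 5 at one usual care center: the SD of the shift was 0.009 to 0.044. The largest single shift was 0.17, at ρ = 0.3, where the SE is 0.30.
- The SE ran from 0.16 to 0.30 over these settings and barely changed with the adjustment.

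**Step 3. Type I error if site-by-time variation exists but is not modelled.** For one change contrast, in units of the variance in change:

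- Variance the model assumes: v₀ = 1/n_E + 1/n_C
- Actual variance: v = (1 − p) × v₀ + p × [1 + Σ(n_j/n_C)²]
- Type I error: 2 × [1 − Φ(1.96/√(v/v₀))]

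For 39 vs 8/8/7, v₀ = 1/39 + 1/23 = 0.0691 and the bracket is 1 + 177/529 = 1.335. At p = 5%, v = 0.95 × 0.0691 + 0.05 × 1.335 = 0.132, so the SE ratio is √(0.132/0.0691) = 1.38.

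For 67 vs 18/14/11, v₀ = 1/67 + 1/43 = 0.0382 and the bracket is 1 + 641/1849 = 1.347. At p = 5%, v = 0.95 × 0.0382 + 0.05 × 1.347 = 0.104, so the SE ratio is 1.65.

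| Assumed share p | 39 vs 8/8/7: SE ratio | Type I error | 67 vs 18/14/11: SE ratio | Type I error |
|---|---|---|---|---|
| 1% | 1.09 | 7% | 1.16 | 9% |
| 2% | 1.17 | 9% | 1.30 | 13% |
| 5% | 1.38 | 16% | 1.65 | 23% |
| 10% | 1.68 | 24% | 2.10 | 35% |

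The joint test over all three time points, simulated with 8,000 runs per setting, gave 8%, 10%, 21% and 37% for 39 vs 8/8/7, so the single-contrast figures are not the high end.

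**The case against.** The strongest case against has four parts.

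**A fixed effect need not mean a main effect only.** The plan introduces time and group as fixed effects and adds their interaction afterwards, and a condensed article may leave a site × time term to a fuller document. This is fair as far as it goes. The point is about the analysis as stated, whose stated purpose needs a term that is not mentioned.

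**A reader might infer that the check can never alter the estimate. The documents do not support that.** The cohort is open, 18 children lack T0, and disability status, one of the covariates, is reassessed every 6 months. Each breaks exact invariance. Step 2 shows the effect of the late entrants. A simulation with a time-varying covariate on complete data gave shifts of at most 0.04 against an SE of 0.26. Exact invariance holds for complete data with covariates fixed over time; otherwise the shift is usually small.

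**A reader might also infer that the check detects no site differences. That is too strong.** Two contrasts among the usual care centers stay estimable, so the first stated purpose is partly met, for levels. The redundant column does no harm in itself, because the group main effect is not the intervention effect.

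**The primary test is not shown to be too liberal.** That needs site-by-time variance above zero, and the protocol gives no value. It gives reasons why the variance could be small: one governing organization, the same licensing, cost, staffing ratios, meal and nap protocols, and the same provincial framework. If the target is only these four centers, taken as fixed, the inflation does not arise. This stands, so the error rates above are conditional.

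**Conclusion.** The concern holds for the second purpose of the site analysis. As stated, the analysis cannot show how far differences between usual care centers influence the group × time result: its shift is zero on complete data, and typically (as an SD) 0.001 to 0.044 against an SE of 0.16 to 0.30 with the late entrants, for an assumed site SD of 0.5. This part is algebra and does not depend on unknown variances.

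The understated error is conditional. It applies to a program-level claim and depends on the assumed site-by-time share and the assumed split of usual care children. Over shares of 1% to 10% the nominal 5% becomes about 7% to 24% for the children with all three Wave 1 assessments, and 9% to 35% if all those now enrolled contributed a change.

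No analysis removes the underlying limit. With one experimental center, program and center are confounded, and variation among outdoor-focused centers cannot be estimated. The limitations section discusses non-randomization, self-selection and access, but not this. It is a should-fix point: the primary model can stay, but its site check and the wording of its conclusion need to change.

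**What to change.** 1. Keep the primary group × time model.
2. Replace the site sensitivity analysis with a model containing time, four-level site and site × time, without the group terms (12 columns, full rank). Report from it:
   - change at the experimental center minus the equally weighted mean change of the three usual care centers;
   - the three separate contrasts of the experimental center with each usual care center;
   - the spread in change among the three usual care centers, as the yardstick for the first contrast.
3. Show how the primary CI widens over a range of assumed site-by-time variances, labelled as conditional. For shares of 1% to 10% the SE ratios in the table run from 1.09 to 1.68, or from 1.16 to 2.10 with the larger sample. Do not report a single CI built on a variance estimated from the usual care centers: it would rest on 2 df and would borrow that variance for the one experimental center.
4. Add to the limitations that program and center effects cannot be separated with one experimental center, and word the conclusion as this center compared with these three.

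The cost is a few extra contrasts on data already being collected, and a narrower claim. Interim analyses follow each year and the first year is complete, so the change is best made before further results are reported.
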